## Serious AEs

An SAE form should be completed and sent to the CI within 24 hours. However, relapse and death and hospitalisations for elective treatment of a pre-existing condition do not need reporting as SAEs. All SAEs should be reported to the REC where, in the opinion of the Chief Investigator, the event was:

‘related’, i.e. resulted from the administration of any of the research procedures; and‘unexpected’, i.e. an event that is not listed above (ELABS Harms) as an expected occurrence

Reports of related and unexpected SAEs should be submitted by the Sponsor within 15 days of the Chief Investigator becoming aware of the event, using the NRES SAE form for non-IMP studies. Local investigators should report any SAEs as required by the National Research Ethics Committee and/or local Research & Development Office. All SAE’s and AE’s will be reported to TSC. AE reports will be sent out to all PIs following each TSC meeting. Receipt of these reports will be signed for in local Trial File.

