#### Harms

The most serious adverse event in the use of a laser is retinal burn, which may lead to permanent blindness. All laser clinics/sites are subject to government guidelines. The Health and Safety at Work Act 1974 and the Management of Health and Safety at Work Regulations 1999 require the employer and employee to undertake reasonable and practical health and safety measures. This serves to minimise this risk though designation of a “Laser Controlled area”, as defined by the Control of Artificial Optical Radiation at Work Regulations (AOR) 2010, performance of a risk assessment, publication of local rules and use of Personal Protective Equipment. There are no necessary regulatory approvals. All laser sites in the study have appropriate laser safety precautions in place, as determined by the local Laser Protection Advisors.

The adverse events from PDL treatment include, but are not limited to:

BlistersScabbingExcessive oedemaExcessive pigmentation changesExcessive PainWorsening of the scarOther

The scar might be fragile at this early stage but blistering is unlikely. Redness and/or oedema are to be expected and usually resolve within 7 – 10 days. Changes in pigmentation are often caused by the burn injury and the subsequent scarring; hypopigmentation is often inevitable in burn scarring. Hyperpigmentation resolves or can be treated at a later stage using Q-switched lasers. There have been few documented occurrences of worsening of the scar using PDL.

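### Death is exempted from serious adverse event reporting with no clear limit on cause, and 'unexpected' is defined against an open-ended harms list

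*Protocol article*

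**What the plan says.** Under Harms reporting procedures, every adverse event is to be reported to the CI, with its severity, possible causality and whether it was anticipated. Staff then follow one of two procedures. Non-serious events are recorded in the participant's notes. For serious events, "An SAE form should be completed and sent to the CI within 24 hours".

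The Serious AEs section then makes an exception: "relapse and death and hospitalisations for elective treatment of a pre-existing condition do not need reporting as SAEs".

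A second filter applies to the REC. "Reports of related and unexpected SAEs should be submitted by the Sponsor within 15 days", where the CI judges whether an event is related and unexpected. Unexpected means "an event that is not listed above (ELABS Harms) as an expected occurrence". The same section sends all serious and non-serious events to the Trial Steering Committee (TSC), and has local investigators report serious events as the ethics or local research office requires.

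The Harms section, which serves as the reference, contains three kinds of statement:

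- Prose on the worst case: "The most serious adverse event in the use of a laser is retinal burn, which may lead to permanent blindness".
- A list introduced by "The adverse events from PDL treatment include, but are not limited to", with these items (run together in the extracted text): "BlistersScabbingExcessive oedemaExcessive pigmentation changesExcessive PainWorsening of the scarOther".
- Prose on likelihood: "Redness and/or oedema are to be expected and usually resolve within 7 – 10 days". It also calls loss of pigment often inevitable, blistering unlikely and worsening of the scar seldom documented.

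**The concern.** A serious adverse event rule should ensure that the gravest events reach the people who can act on them, quickly and without local interpretation. Here the exemption covers the gravest outcome of all. As worded, a site that receives news of a death can conclude that no form is due. Because the REC rule speaks only of serious adverse events, a death taken out of that category can drop out of the REC route too, even if a laser session caused it.

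The expectedness test has a milder problem. It decides which related serious events go to the REC, but it points to a section that mixes an open list, a catch-all item and remarks on likelihood. Two careful readers could classify the same event differently. At stake are prompt ethical oversight and consistent classification across sites. The DM(E)C is also affected, since one of its main roles is to assess unexpected adverse effects and the article gives no other definition of that term.

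**Working it through.** No arithmetic applies, because no figure in the plan depends on this rule. The check is to set the provisions side by side.

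**Step 1: does any qualifier limit the exemption for death?** The exemption joins three items: relapse, death, and hospitalisations for elective treatment of a pre-existing condition.

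- The words on elective treatment can attach only to the hospitalisations.
- The closing words on a pre-existing condition could be stretched back over all three items. Even then, a death attributed to such a condition would be exempt, and the attribution would be made before any form is filed.
- Neither reading says that treatment-related deaths stay reportable. Relapse is not defined for a burn scar anywhere in the article.

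**Step 2: which routes remain?**

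| Route (section) | Stated deadline | Death, exemption as printed | Serious retinal burn |
|---|---|---|---|
| General report to CI (Harms reporting procedures) | None | Yes | Yes |
| SAE form to CI (Serious AEs) | 24 hours | Can be missed | Required; expectedness plays no part |
| Sponsor report to REC (Serious AEs) | 15 days | Can be missed, even if related | If related, depends on how Harms is read |
| Report to TSC (Serious AEs) | None | Yes, as an adverse event | Yes |

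The exemption removes exactly the two routes that carry a deadline. What remains for a death is the general duty to tell the CI. The section stating that duty sends staff on to procedures of which one is for non-serious events and the other exempts death. The TSC route has no deadline. If it follows scheduled meetings (an assumption), the Trial Steering Committee section gives months 2, 12, 24 and 33, so gaps of 10, 12 and 9 months. Recruitment feasibility gives about 4, 8, 12 and 16 months into recruitment, so gaps of about 4 months. Neither is expedited.

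**Step 3: does the expectedness reference separate expected from unexpected?** Three readings are possible.

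- *Reading A: anything on the Harms list is expected.* The item 'Other' then admits any event, and the test excludes nothing.
- *Reading B: anything mentioned in Harms is expected.* Retinal burn is then expected as well, through the opening prose.
- *Reading C: only what Harms describes as expected counts.* That gives redness and/or oedema, arguably with loss of pigment. Blistering, worsening of the scar and retinal burn are then unexpected.

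The definition requires an event to be listed as an expected occurrence, which favours Reading C. But Harms has no list under that label. Its only list is of adverse events in general, and it includes blisters and scar worsening, which the following prose describes as unlikely or seldom documented. Reading C is the better one; the text does not secure it.

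**The case against.** The exemption looks like badly joined template text, and no sensible CI would ignore a death. Relapse of a pre-existing condition is intelligible if the last words cover all three items. That may explain the origin of the wording, but no such limit is printed, and a reporting rule should not depend on sites departing from it.

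The objection has more force against broader claims. A reader might infer that no related serious event could ever reach the REC, because 'Other' makes everything listed. The documents do not support that: the event must be listed as expected, 'Other' names no event, and the CI exercises judgement. A reader might also infer that a retinal burn counts as expected and escapes reporting. It is not on the list, it is never called expected, and a serious case needs the 24-hour form regardless.

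Nor can it be said that the DM(E)C has no route to unexpected effects, or that the objective on the adverse effect profile must miss the worst events. The DM(E)C is given that role directly, and nothing ties its access to the REC test. All adverse events go to the CI, and serious and non-serious events alike go to the TSC. Local reporting requirements may also catch some cases. These points stand and confine the finding to the routes marked in the table.

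**Conclusion.** The point holds in a limited form, and its main part needs correcting.

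**Main part.** The printed rule lets any death, including a treatment-related one, miss the 24-hour form and the 15-day REC report. This conflicts with the general duty to report all adverse events to the CI and leaves only routes without a deadline. The conclusion rests on the wording as printed. A qualifier may have been lost in drafting, but none is shown.

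**Secondary part.** The reference for unexpected is ambiguous. The most natural reading works, but a literal reading of the catch-all does not, and the status of retinal burn is left to interpretation. This calls for clarification; it does not show that the REC test can never be met.

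No numerical size can be given. The documents contain no expected rate of death or of serious laser injury, and the conclusion needs none.

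**What to change.** - In Serious AEs, remove death and the undefined relapse from the exemption, so that deaths go through serious adverse event reporting. The exemption for elective hospitalisation can stay.
- Replace the general pointer to Harms with a closed list of the events that the sponsor regards as expected, without 'Other'. The list should make clear where eye injury falls; that classification is for the sponsor to state.
- Reconcile Harms, Harms reporting procedures, Serious AEs and the DM(E)C section so that expected and unexpected have one meaning throughout.

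The cost is a wording amendment, circulated to sites through the amendment process already described under Ethics approval and registration. Extra reporting should be negligible in a scar trial planning to recruit 150 participants. Design, sample size and analysis are unaffected.

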### Retention

All attempts will be made to collect all outcome measures on all participants, regardless of whether they adhered to their treatment. Outcome measures are collected at clinic appointments that form part of their usual care and so it is anticipated that retention will be good. The study design has allowed for up to 20% of participants not to supply data within the sample size considerations.

If a participant does not attend their clinic appointment, this will be rearranged within the next couple of weeks. If this does not happen, attempts will be made to collect those outcome measures that can be collected by phone, prioritising the collection of the primary outcome. If it is not possible to collect data then, where possible, the reason why will be recorded to help with populating the CONSORT flow chart.

Participants in the laser arm of the trial will receive three treatment sessions. A record of attendance at treatment sessions will be kept, and whether they actually received the treatment. If they didn’t receive treatment, the reason why will be recorded, where available.

In consideration of the current COVID crisis, further consideration is made as to the conduct of the study. The primary outcome of patient-rated POSAS can be obtained over the phone when the patient is unable to attend. The observer-rated POSAS can be performed using photos; though this is less reliable particularly for evaluation of thickness and pliability. Patient photographs are also not generally of a sufficient standard. Similarly, the healthcare resource data, patient perception question and qualitative interview can be performed by telephone. Most standard care treatments can be managed remotely, whereas the laser treatment and colour measurement would require the attendance of the patient.

### Data management

The data collection tool for this study will be paper CRFs. Data will be entered directly onto the CRFs and considered a source document. The data collection may be conducted by the CRN nurses, the PIs or the HCP involved in the scar assessment. There may be variation between sites, and this will be detailed in the SOPs for each site.

The recruitment sites will store all original signed informed consent forms (model consent form in the *Extended data*
^
71
^). All data will be entered electronically onto a database by the Trial Coordinator at the sponsor site or at the participating site where the data originated. This database (REDCap Cloud) is managed by the CTU. Original study forms will be entered and kept on file at the participating site. Copies of 10% of completed forms will be sent by post to the trial coordinator in batches for checking. The CTU will produce reports on data completeness, flag issues and supervise the Trial Coordinator.

All data is recorded and kept in project file for quality control and will be monitored by the sponsor through the Trial Coordinator. Personal data, as defined by General Data Protection Regulation, is not disclosed without written consent. All personal information is kept for the duration of the study and archiving period, after which it will be destroyed. Data archiving costs are included.

### Data Monitoring

#### Formal committees

##### Trial Steering Committee

TSC provides overall supervision for, and regular, impartial oversight of, the study. TSC meetings are scheduled to follow shortly after DM(E)C meetings so that reports from that group are considered if appropriate. TSC meets at 2 months to approve the final protocol, 12 months to review study processes and recruitment, 24 months to approve the statistical analysis plan and 33 months to discuss results and dissemination. At 12 months (9 months into the recruitment phase), TSC review study progress and recommend whether to continue based on likelihood of achieving the recruitment target within timescale. The TSC will compose of an independent Chair, a patient representative, a statistician, a scientist with laser expertise, a clinician with scar and laser expertise and a sponsor representative. Minutes of meetings should be retained in the study master file.

##### Data Monitoring (and Ethics) Committee (DM(E)C)

The DM(E)C will monitor the study and make recommendations to the Trial Steering Committee (TSC). The main consideration is the safety, rights and well-being of the trial participants. The DM(E)C establish their terms of reference at their first meeting. Their main roles are to assess any unexpected adverse effects in the trial and consider new evidence on the safety and effectiveness of laser treatment. General issues such as conduct of the research, compliance to the protocol, recruitment rates, and the data integrity/quality will be discussed. They will also consider any reasons to stop or modify the trial. The DMEC will comprise of two statisticians with experience in study design. Minutes of meetings are retained in the study master file.

### Interventions

#### Pulsed Dye Laser (treatment arm)

There are two models of PDL from different manufacturers; Cynergy (Cynosure, West-ford, MA, USA) and the Vbeam (Syneron Candela, USA). The settings to be used are:

10 mm, spot size0.5 ms, pulse duration5 – 9 J cm^-2^, energy fluenceApprox. 10% overlapSingle pass

Laser treatment follows assessment and is performed by a trained laser operator. Where multiple scars are present, the laser operator treats the study scar. Other non-contiguous scars may be treated within the limit of total treated area deemed suitable. The energy is selected to produce a degree of purpura during treatment without the presence of skin blanching. The skin response is instantaneous and should be dark purple to black. Blanching (or whitening) in the treatment area suggests over-treatment and is to be avoided. If the operator is unsure, a pause of up to a couple of minutes can be adopted to verify the skin response. Once the desired response is observed, the operator should treat the entire trial scar.

Skin cooling is administered during the treatment. Almost all patients cope with the pain without any anaesthesia; neither topical nor local. The PPI group agreed that pain, though sensate, is not an issue. If necessary, topical anaesthesia is offered and recorded, if used. This provides comfort for the participant and minimises collateral damage. Post-treatment photographs are taken after treatment. Cool Aloe Vera gel may be offered to the participant to apply to the treated area after treatment and its application will be recorded. This may help to soothe any discomfort and reduce the residual heat. The treated areas do not require dressing and after-care information is provided. The patient is advised to avoid perfumed cosmetics, any abrasive drying, tight-fitting clothes, and any strenuous exercise or swimming in chlorinated water for 72 hours. This will include the use of any pressure garments.

At subsequent visits, the participants are asked to report on any adverse effects of the treatment. The previous settings should be used to start the treatment but the operator may increase the energy in 0.5 Jcm^-2^ steps until a similar response to the previous visit is achieved. All laser settings are recorded for each visit.

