### Eligibility criteria

#### Inclusion criteria

NHS patients, with burn injuries >1% Total Body Surface Area, are eligible if they have been treated with skin grafts or had conservatively managed burn wounds or donor sites that:

have delayed healing of greater than 14 days.have potential for hypertrophic scarring.are suitable for scar management therapy.

The scar must be within 3 months of healing, where healing time-point is defined by the Healthcare Professional (HCP) during wound management. This time to healing must be for the study scar that is included in the study. The combination of excessive redness with increased thickness and/or hardness provides clear indication of potential scarring, as defined by HCP assessing for scar management.

Where there are multiple scars, the scar having the greatest impact, as reported by the patient, will be included in the trial. Only one scar per patient will be included, and this scar will be identified prior to randomisation. No other scars will be treated with laser until after the study ends for the participant (i.e. post week 26 visit).

The approximate size of the study scar would be anything up to 200 cm^
2
^. The size or extent of laser treatment would be determined by or in discussion with the laser operator. The minimum size for the study scar would be 4 cm × 4 cm. The latter is the size of the scar region of interest (ROI) that is used for the colorimeter assessment. In order to ensure the same scar is being treated/assessed on each occasion, the scar will be identified and logged using clinical photography and skin markers, where present.

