#### Outcome measures

Scar quality and all measures and questionnaires assessed by the patient is for the study scar as a whole. Additionally, Observer POSAS will be performed for the study scar as a whole. Only the colorimeter measurement is carried out for the Scar ROI.

Burn scar quality is assessed using POSAS^
64
^; the most commonly used scar assessment scale^
65
^ and the only one including the patient’s perception of the scarring. POSAS v2.0 has been shown to be a reliable and feasible tool for the evaluation of scars^
66,67
^. It consists of two parts: a Patient Scale and an Observer Scale. Both scales contain six items that are scored numerically on a ten-step scale (1 – 10). Each makes up a ‘Total Score’, which ranges from 6 – 60 where a higher score reflects reduced scar quality. The mean POSAS scores for scar quality at the primary endpoint of 6 months are compared between trial arms. A reduction in the POSAS score determines whether the proposed intervention improves the scar quality.

The impact on the scarring on the psychological well-being of the patient is assessed using the CARe scale^
68
^. The Adult Scale consists of 53 items which cover 14 individual scales; 12 of which fulfilled Rasch and traditional psychometric analyses. These will be analysed in accordance with guidance provided by the CARe team.

QoL is further assessed by SF-12 in order to calculate Quality Adjusted Life Years (QALY). The SF-12 is a multi-purpose short form version of the SF-36 and s a generic measure of health status. The SF-12 physical (PCS-12) is scored using norm-based methods. The scale is transformed to have a mean of 50 and standard deviation of 10.

The resource implications of PDL will be captured in two ways. Secondary care resource use (e.g. clinic visits, resource requirements for PDL delivery) will be collected using a pro forma within the trial case report form (CRF). Primary care resource use (e.g. GP visits) and additional personal expenditures (e.g. burn care products, travel) will be collected using a patient completed questionnaire. This will be based on questionnaires used in previous clinical trials and adapted for the specific study requirements. Secondary care resource use is collected from routine clinic data. Wider costs, such as primary and social care resource use, are collected using direct patient self-reports. Patient-incurred costs are collected at baseline and follow-up.

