#### Data collection methods

##### Scar assessment

At each assessment, the participant acclimatises for at least 20 minutes to allow blood flow and skin temperature to equilibrate. The participant remains seated for the duration of assessment. Where the participant has multiple, non-contiguous scars at different anatomical locations, the “worst” scar, as identified by the participant, is assessed and included in the study. It would be prudent to be mindful to avoid areas where they may be a future need for surgery such as areas where contractures are beginning to form.

Whichever treatment group the patient is assigned to, each time they return for assessment, **the same area of hypertrophic scarring must be assessed and treated.** This will be known as the ‘Study Scar’. The ‘Study Scar’ is the scar that the patient, and the designated research team member at weeks 0 and 26, must assess and consider for all their visits. It is important that the participant is aware of this.

The ‘Study Scar’ and each ROI must be selected at the enrolment appointment. Firstly, the scar to be treated and assessed must be identified as a whole; this will be known as the ‘Study Scar’. This will be chosen in agreement with the participant. Where the participant has multiple, non-contiguous scars at different anatomical locations, the ‘Study Scar’ is agreed and included in the study. It would be prudent to be mindful to avoid any area for the ‘Study Scar’ where they may be a future need for surgery such as areas where contractures are beginning to form. The ‘Study Scar’ can be up to about 200 cm^
2
^ in size. This limit has been determined as the conventional total area of burn scar that would normally be treated by laser in one visit. Regardless of study group, the limit or guidance for size of ‘Study Scar’ area is the same.

Only part of this hypertrophic scar must then be selected as the ‘Scar ROI’. This should be the part of the burn scar that is the **
*most problematic to the participant.*
** This is typically excessively red, thickened and firm to touch compared to normal, unburnt skin. An area 4 cm x 4 cm is the optimal size for selection. This will the scar region of interest or ‘Scar ROI’ and this is the area that will be used for the **ColorMeter measurements only**.

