#### Standard care (control arm)

Both arms of the trial will be given standard care. The choice of standard care for this trial includes; moisturisation and massage up to 2 – 3 times per day (as directed by the HCP; where maintenance of hydration is required) ± silicone gel treatment ± pressure garments, dependent upon scar maturation.

The control arm receives standard care only. The treatment arm receives a course of three PDL treatments at intervals of 6 weeks, in addition to standard care treatment, as detailed in Table 2. All follow-ups allow ± 1 week to allow for clinic administration.

The following treatments are not permitted for the study scar only and will mean that the participant is withdrawn from the study: Fractional ablative laser, micro-needling, scar revision and/or grafting.

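### The protocol both bars and permits laser to non-study scars before week 26; the permission reaches the PDL arm only and could affect the cost-utility comparison

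*Protocol article*

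**What the plan says.** Inclusion criteria in the protocol article allows one study scar per participant and states: "No other scars will be treated with laser until after the study ends for the participant (i.e. post week 26 visit". It makes no exception by arm or by treated area.

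Under Interventions, the section Pulsed Dye Laser (treatment arm) first directs the operator to the study scar when there are several scars, then adds: "Other non-contiguous scars may be treated within the limit of total treated area deemed suitable".

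Four other sections bear on the point:

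- **Standard care (control arm):** "The control arm receives standard care only", while "The treatment arm receives a course of three PDL treatments at intervals of 6 weeks". Its list of treatments that lead to withdrawal applies to the study scar only and does not name PDL.
- **Scar assessment:** at each visit "the same area of hypertrophic scarring must be assessed and treated". It sets no rule for other scars.
- **Outcome measures:** "Scar quality and all measures and questionnaires assessed by the patient is for the study scar as a whole". The same section describes SF-12 as "a generic measure of health status" and lists "resource requirements for PDL delivery" among the secondary-care resource use to be collected.
- **Economic analysis:** the primary economic analysis is a cost-utility comparison of PDL with standard care, with QALYs from SF-6D.

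**The concern.** Site staff have two published instructions that cannot both guide practice. An operator who follows the intervention section may laser other scars at a trial session, and one who follows the eligibility section may not. Both would be acting in good faith, so practice could differ between sites.

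Extra lasering could happen in one arm only, because controls attend no laser sessions before week 26. The contrast between arms would then no longer be PDL to one study scar against none. It would be PDL to the study scar, plus an undefined amount to other scars in some participants, against none.

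The clinical scar outcomes are largely protected because they refer to the study scar or its region of interest. The exposed part is the economic evaluation. It is a secondary analysis, but cost-effectiveness is named in the Research question. Extra PDL could enter it through delivery cost and through health utility.

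**Working it through.** The claim is a conflict of text, so the main check sets the rules side by side. The only arithmetic gives an upper limit on how many sessions the conflict covers.

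**1. Do the two rules cover the same people and period?**

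| Source | Rule for non-study scars | Period | Who |
|---|---|---|---|
| Inclusion criteria | No laser | Until after the week 26 visit | All participants |
| Pulsed Dye Laser (treatment arm) | Laser allowed, subject to suitable total area | Trial laser sessions | PDL arm |

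Three treatments 6 weeks apart, starting at week 0, fall at weeks 0, 6 and 12. Follow-up duration agrees: it puts about 3 months between the last treatment and the primary endpoint. All three sessions therefore precede week 26, and the permission cannot be read as post-trial care. The rules overlap and are opposed.

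**2. Does other text settle it?** No. Scar assessment fixes the study scar across visits and is silent on other scars. The list of treatments that are not permitted concerns the study scar only. Both sentences are current text.

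**3. Can the situation arise?** Yes. Inclusion criteria, Scar assessment and the laser section all provide for participants with several scars. The minimum study scar is 4 cm × 4 cm = 16 cm². Scar assessment gives about 200 cm² as the area normally treated in one visit. If that is the area limit meant in the laser section (an assumption), up to 200 − 16 = 184 cm² could go to other scars in the smallest case, and nothing in a participant whose study scar fills the limit.

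**4. How many sessions fall under the conflict?** The recruitment target reproduces: 120 / (1 − 0.20) = 150.

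- PDL arm at 1:1: 150 / 2 = 75.
- Planned PDL sessions: 75 × 3 = 225. Control sessions: 0.
- With 60 per arm: 60 × 3 = 180. This lower figure is loose, because Retention describes the 20% as participants who supply no data, not as missed laser sessions.
- The share of participants with another scar is not given. Assuming 10% to 50%: 225 × 0.10 = 22.5 and 225 × 0.50 = 112.5, so about 23 to 113 sessions, before any area limit is applied.

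**5. Which outcomes are exposed?**

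- *Patient POSAS, observer POSAS, colorimetry:* tied to the study scar or its region of interest; not directly affected.
- *Cost:* PDL delivery resources are collected, so extra lasering could add to PDL-arm cost. The document does not say whether cost varies with treated area.
- *QALYs:* Outcome measures says patient questionnaires refer to the study scar, which covers SF-12, yet it also calls SF-12 generic. That a generic health measure cannot readily be confined to one scar is an inference of this review and is not stated in the protocol.

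No effect size can be computed. The number of participants with several scars, the relation of cost to area, and any SF-6D effect are all missing.

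**The case against.** The best case against accepts the conflict and disputes its importance.

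- **The consequence is slight and unproven.** The primary outcome is not directly touched. Extra lasering would be given at sessions already planned, and Recruitment feasibility describes PDL as quick, so added cost could be nil. This stands as a limit on size.
- **The QALY route runs against the statement that patient questionnaires concern the study scar.** This stands in part. The route remains arguable because SF-12 is generic, but it rests on inference.
- **Costs would be captured.** A case report form collects PDL resource use, laser settings are recorded at each visit, and photographs are taken after treatment. This helps with cost. The article does not say that the scar and area treated are recorded, so PDL to other scars could not clearly be separated out.
- **Sites can satisfy both rules by never lasering another scar,** since one rule is categorical and the other only permissive. That is true, but an operator who uses the permission breaches the prohibition, and nothing tells the operator which rule prevails. Site initiation visits and operating procedures might do so; their content is not shown.
- **The session counts say little.** Agreed. They mark the extent of the conflict and nothing more.

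None of this removes the contradiction or the fact that extra PDL would fall in one arm.

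**Conclusion.** The concern holds. The article forbids and permits the same act in the same period, and no other text resolves it. This is an error in the text as it stands; it is not detail left to a fuller document. Confidence is high on the contradiction and on its one-arm reach. The effect on the cost-utility comparison is only possible: its sign and size are unknown, and it may be negligible.

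The upper limit is about 225 PDL-arm sessions, against none in controls. The narrower range of about 23 to 113 depends on the assumed 10% to 50% with another scar. The contradiction itself depends on none of these figures. It should be fixed because the correction is trivial and, once extra PDL has been given without a record of scar and area, its contribution could not be separated out.

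**What to change.** Before the first treatment, delete the sentence "Other non-contiguous scars may be treated within the limit of total treated area deemed suitable" from Pulsed Dye Laser (treatment arm), so that the prohibition in Inclusion criteria governs at every site. Study status describes recruitment as imminent in November 2021, so on the document's own account there was time to do this.

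The cost is one deleted sentence and an amendment sent to sites by the route in Ethics approval and registration. PDL-arm participants with other scars wait until after week 26 for laser to them, as Inclusion criteria already says.

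If extra lasering is to be kept, amend Inclusion criteria to match, record the scar and area treated at each session, and report the cost and QALY contrasts as including PDL to non-study scars.
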